# The use of Lutetium-177 PSMA radioligand therapy with high dose rate brachytherapy for locally recurrent prostate cancer after previous definitive radiation therapy: a randomized, single-institution, phase I/II study (ROADSTER).

**DOI:** 10.1186/s12885-023-10851-0

**Published:** 2023-04-20

**Keywords:** Prostate Cancer, Isolated Local Failure, Radiorecurrent Prostate Cancer, High Dose Rate Brachytherapy, Lutetium-177, Prostate Specific Membrane Antigen, Positron Emission Tomography, Radioligand Therapy

## Abstract

**Background:**

Isolated local failure (ILF) can occur in patients who initially receive definitive radiation therapy for prostate cancer. Salvage therapy for ILF includes high dose rate (HDR) brachytherapy. Prostate Specific Membrane Antigen (PSMA) Positron Emission Tomography (PET) can accurately detect ILF and can exclude extraprostatic disease. Lutetium-177 PSMA Radioligand Therapy (RLT) is a novel treatment for prostate cancer that can target prostate cancer accurately, while sparing radiation dose to normal tissues.

**Methods:**

ROADSTER is a phase I/II randomized, single-institution study. Patients with an ILF of prostate cancer after definitive initial radiation therapy are eligible. The ILF will be confirmed with biopsy, magnetic resonance imaging (MRI) and PSMA PET. Patients will be randomized between HDR brachytherapy in two fractions (a standard of care salvage treatment at our institution) (cohort 1) or one treatment of intravenous Lutetium-177 PSMA RLT, followed by one fraction of HDR brachytherapy (cohort 2). The primary endpoints for the phase I portion of the study (n = 12) will be feasibility, defined as 10 or more patients completing the study protocol within 24 months of study activation; and safety, defined as zero or one patients in cohort 2 experiencing grade 3 or higher toxicity in the first 6 months post-treatment. If feasibility and safety are achieved, the study will expand to a phase II study (n = 30 total) where preliminary efficacy data will be evaluated. Secondary endpoints include changes in prostate specific antigen levels, acute toxicity, changes in quality of life, and changes in translational biomarkers. Translational endpoints will include interrogation of blood, urine, and tissue for markers of DNA damage and immune activation with each treatment.

**Discussion:**

ROADSTER explores a novel salvage therapy for ILF after primary radiotherapy with combined Lutetium-177 PSMA RLT and HDR brachytherapy. The randomized phase I/II design will provide a contemporaneous patient population treated with HDR alone to facilitate assessment of feasibility, tolerability, and biologic effects of this novel therapy.

**Trial registration:**

NCT05230251 (ClinicalTrials.gov).

## Background

Prostate cancer is a major male health issue, with over 1.4 million new cases of prostate cancer diagnosed and 375,000 new prostate cancer deaths in 2020 worldwide [1]. Many patients may choose radiation therapy for treatment of prostate cancer but despite improvements in treatment, progression or recurrence can occur, with approximately 20–47% of men having a rise of prostate specific antigen (PSA) that meets the Phoenix criteria for biochemical failure (BCF) at 15 years post-treatment [2, 3]. One scenario of clinical importance is isolated local failure (ILF), without evidence of metastatic disease. In a meta-analysis of patients with prostate cancer recurrence post-radiation, at a median follow-up of 11 years, there was a 7.2% and 13% ILF rate for intermediate-risk and high-risk prostate cancer, respectively [4]. In this analysis, while most patients developed metastases from clinically recurrence-free state, the presence of ILF was associated with worse metastasis-free survival (MFS) in intermediate- and high-risk patients, and worse prostate cancer-specific survival and overall survival (OS) in high-risk patients. Furthermore, there was some evidence that a “second wave” of distant metastases could result after ILF in these patients.  Local failure in these trials was defined using clinical examination and conventional imaging and likely underestimates the proportion of men with ILF.

There are several potentially curative treatment options for patients with ILF, including salvage radical prostatectomy (RP), as well as prostate directed ablative therapies such as cryotherapy, high intensity focused ultrasound (HIFU), and salvage radiotherapy options such as stereotactic body radiation therapy (SBRT), low dose rate (LDR) brachytherapy or high dose rate (HDR) brachytherapy. In a recent meta-analysis comparing these options, the chances of recurrence-free survival (RFS) were similar, with approximately half of patients with durable disease control with the different salvage techniques [5]. In a multi-institutional, prospective trial assessing the role of LDR brachytherapy in a highly selected population, the 10-year BCF rate was 46%, with only 5% of the patients having signs of ILF after salvage brachytherapy [6]. Collectively, these results suggest that a significant proportion of patients with presumed ILF on conventional staging scans (computed tomography, bone scintigraphy, magnetic resonance imaging) at the time of salvage therapy may already have disease outside the prostate.

Prostate-specific membrane antigen positron emission tomography (PSMA PET) has been used more recently as a tool to detect prostate cancer recurrence after radiation treatments. In this setting, PSMA PET has been shown to change the management plan in a majority of patients when compared to the management plan based on conventional imaging alone [7]. By identifying men with extra-prostatic disease not evident on conventional imaging, PSMA PET/CT could result in better selection of patients with true ILF. In addition to using PSMA PET for the diagnosis of prostate cancer, PSMA-targeting radioligand therapies (RLTs) have been developed and have shown benefit in the metastatic, castrate-resistant prostate cancer (CRPC) setting. In particular, Lutetium-177 (Lu-177) PSMA RLT has been shown to improve survival outcomes in the PSMA PET positive, CRPC setting and results in significant cytolytic activity and PSA response [8].

Lu-177 PSMA RLT emits beta particles with a maximum energy of 497 keV, which limits the range of these particles in tissue to less than 2 mm [9]. Most studies report a delivered dose to the tumor of 2–6 Gy per GBq of Lu-177 PSMA RLT administered, although this dose can range between 1.4 and 14.5 Gy per GBq [10]. In comparison, the dose delivered to the kidneys, bone marrow, salivary glands, and lacrimal glands has been reported as 0.4-1.0 Gy per GBq, 0.01–0.1 Gy per GBq, 0.6–1.4 Gy per GBq, and 1.0-2.8 Gy per GBq, respectively. Thus, a single dose of 6.8 GBq could provide doses to ILF in a range similar to that delivered with a fraction of HDR brachytherapy with anticipated low dose to organs at risk that are typically limiting in the setting of salvage radiotherapy, i.e., the bladder and rectum.

We hypothesized that a theragnostic combination targeting PSMA may improve outcomes and reduce toxicity in men with suspected ILF after definitive radiotherapy. Specifically, use of a diagnostic PSMA-targeting agent will improve our ability to select men with a high probability of ILF. The use of a PSMA-targeting RLT would then allow the selective treatment of the site of ILF as well as potential extra-prostatic disease not detectable even with the diagnostic PSMA PET imaging. In ROADSTER, we aim to assess safety and feasibility of adding Lu-177 PSMA RLT in combination with HDR brachytherapy for ILF after definitive radiotherapy. A randomized phase I/II design will be used to provide a contemporaneous cohort of men treated with our institutional standard salvage therapy of two fractions of HDR. Translational endpoints will include acquisition of liquid and tissue biospecimens for the assessment of response biomarkers and assessment of DNA damage and immune activation among the two cohorts.

## Methods

### Inclusion and exclusion criteria

Patients with suspected ILF after radiation will be recruited. Patients must have a BCF per Phoenix criteria at least two years after initial prostate cancer treatment, an intra-prostatic lesion with PSMA PET avidity (Standard Uptake Value (SUV) of 3.0 or greater on a diagnostic PSMA PET/CT), and no evidence of extra prostatic disease.

All patients are required to have a prostate biopsy to confirm ILF at the time of enrolment and have no contraindications for HDR brachytherapy, general anaesthesia, PSMA PET/MRI or Lu-177 PSMA RLT. Contraindications for these procedures include having inadequate marrow function (absolute neutrophil count less than 1.5 × 10^9^/L, platelet count less than 100 × 10^9^/L, hemoglobin less than 90 g/L, or transfusions required in the previous two weeks prior to enrolment); inadequate renal function (estimated creatinine clearance less than 30 mL/min by Cockroft Gault equation); or inadequate hepatic function (total bilirubin greater than 1.5 times the upper limit of normal (ULN) or the alanine aminotransferase greater than 3.5 times the ULN). Patients must not have any ongoing grade 3 or greater GU or GI toxicity (by Common Terminology Criteria for Adverse Events (CTCAE) v4.0) associated with their initial prostate cancer treatment. Patients with previous ablative prostate radiotherapy, i.e., HDR brachytherapy, LDR brachytherapy or SBRT to the prostate, will be excluded. Concurrent or adjuvant ADT at the time of salvage therapy is not permitted; patients given ADT as part of the original primary radiotherapy are eligible.

### Baseline assessment

Patients will be required to complete baseline assessments of toxicity by CTCAE v4.0, quality of life (QoL) related to prostate cancer by the Expanded Prostate Cancer Index Composite (EPIC), and baseline bloodwork to assess marrow, renal and hepatic function. Baseline bloodwork and urine samples will be collected as liquid biomarkers for future biomarker analysis. A hybrid PSMA PET/MRI will be done prior to randomization. As part of the PET/MRI, delayed PET images of the pelvis will be acquired at least 60 min after the PSMA ligand injection. MR images of the pelvis will be acquired, including T2 weighted, diffusion weighted, and dynamic contrast enhanced sequences. Imaging will be read by a certified Nuclear Medicine specialist ([name]) experienced in PSMA PET/MRI and PET/CT interpretation using established interpretation schemes [11, 12]. The MR images will be used for intra-operative HDR guidance for both tissue sampling and selective HDR brachytherapy boosting of the foci of ILF.

### Treatment

The trial schema is given in Fig. 1. Patients will be randomized between cohort 1, consisting of two separate whole-gland plus focal boost prostate HDR brachytherapy treatments (considered a standard salvage treatment in our institution) or cohort 2, consisting of one treatment of Lu-177 PSMA RLT, followed by one treatment of prostate HDR brachytherapy. In both cohorts, the time between the first treatment and the second will be 1–2 weeks.

**Fig. 1 Fig1:**
[figure not shown]
ROADSTER trial schema

Brachytherapy will be performed using transrectal ultrasound (TRUS) guidance, under general anesthesia in a dedicated brachytherapy suite, with intraoperative planning. Pre-procedure PSMA PET/MR images will be fused with intra-operative TRUS images using an in-house developed surface-based deformable algorithm to accurately delineate the areas of ILF. For each HDR brachytherapy treatment, 10.5 Gy will be prescribed to the entire prostate, with a focal boost to 13.5 Gy to the clinical target volume of the primary tumor (CTVp), as defined by the gross tumor volume (GTV) on all available images with a 5 mm expansion to account for microscopic disease. Details on brachytherapy planning objectives are found in Table 1.

**Table 1 Tab1:** Dose objectives for a single HDR brachytherapy treatment

Structure	Dose parameter^1^	Objective (Acceptable)
Prostate	V 90%	Greater than 99% (95%).
	V 100%	Greater than 95% (90%).
	V 150%	Less than 35% (40%).
	V 200%	Less than 11% (15%).
CTVp^2^	V 90%	Greater than 99% (95%).
	V 100%	Greater than 95% (90%).
Urethra	D 0.01 mL	Less than 12 Gy.
Rectum	D 0.1 mL	Less than 8.5 Gy (9 Gy).
	D 1 mL	Less than 6.5 Gy (7 Gy).

^*1*^
*The dose parameter “V X%” refers to the proportion of the structure’s volume receiving at least X% of the prescription dose. The dose parameter “D Y mL” refers to the dose received by the hottest Y mL of the structure.*

^*2*^
*The clinical target volume of the primary tumor (CTVp) is constructed by taking the union of the GTVs, as delineated on MR and PSMA PET, expanding the structure by 5 mm uniformly, then editing the resulting structure to the boundary of the prostate and the urethra.*

Lu-177 PSMA RLT will be delivered in the Department of Nuclear Medicine as per local practice. One dose of 6.8 GBq of Lu-177 PSMA RLT will be administered intravenously, which will deliver an estimated tumor dose of 13.6–40.8 Gy, given the estimated dose of 2–6 Gy per GBq that has been reported in the literature [10]. Patients will be monitored in an outpatient setting afterwards to assess for adverse events and will undergo Single Photon Emission Computerized Tomography (SPECT) / CT scans at three time points: 2–4 h, 24 h, and 48–96 h post Lu-177 PSMA RLT administration for dynamic dose quantification.

### Primary and secondary endpoints

ROADSTER is a phase I/II, randomized controlled trial with safety and feasibility as primary outcomes. The planned accrual for the phase I portion of the study will be 12 patients: six patients in cohort 1 and six patients in cohort 2. Safety of each cohort will be declared if no more than one patient in each cohort experiences a grade 3 or higher CTCAE V4.0 toxicity at 6 weeks or 6 months post-treatment. Feasibility will be declared if 10 or more of the planned 12 patients are successfully accrued and complete the study as per protocol within 24 months of activation. If the initial accrual of 12 men across both cohorts demonstrates both safety and feasibility, the study will expand to the phase II portion, in which 30 men in total will be enrolled and randomized between these two cohorts. Sample sizes were chosen to support measuring the safety and feasibility of this study in the phase 1 and 2 portions. No formal statistical sample size calculation was performed.

Secondary endpoints will include biochemical response, defined as a decrease of PSA by 50% from the baseline level; acute toxicity, defined by changes in CTCAE v4.0 scores; and changes in EPIC QoL scores. These secondary endpoints will be assessed at baseline, 6 weeks after treatment and 6 months after treatment.

### Translational exploratory endpoints

At the time of the second HDR treatment for cohort 1 and the HDR treatment for cohort 2, patients will receive a research prostate biopsy via a transperineal approach under ultrasound guidance. Targeted biopsies of PSMA PET/MR defined lesions will be obtained along with systematic biopsies of the whole gland. These tissue samples are obtained for further translational studies and will assess the effects of HDR brachytherapy in cohort 1 and Lu-177 PSMA RLT in cohort 2 on the prostate cancer ILF.

Blood and urine samples will be collected prior to the first treatment, prior to the second treatment, at 6 weeks after the second treatment and at 6 months after the second treatment, in both cohorts 1 and 2. Patients will have serum PSA, marrow function, renal function and hepatic function bloodwork at 6 months after the second treatment in both cohorts. CTCAE v4.0 toxicity scores and EPIC QoL scores will be done at 6 weeks and 6 months after the second treatment as well.

Regarding the translational biomarkers, the research biopsy specimens will undergo panel-based deoxyribonucleic acid (DNA) sequencing analysis of commonly altered DNA repair pathway and prostate cancer genes, tumor-associated T-cell receptor deep-sequencing (TCR-seq), as well as PSMA expression and gamma-H2A histone family member X (gamma-H2AX) expression, a marker of radiation-induced DNA damage, by immunohistochemistry. Blood plasma will also undergo circulating tumor DNA (ctDNA) sequencing as well as peripheral blood mononuclear cell (PBMC) analysis with TCR-seq and flow cytometry assessing markers of immune activation and radiation-induced DNA damage (e.g., gamma-H2AX). Finally, urine will be collected for urine tumor DNA (utDNA) sequencing.

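### The primary safety rule has two definitions, and the Methods version can miss grade 3+ toxicity after Lu-177 and before, or without, HDR brachytherapy

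*Protocol article*

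**What the plan says.** **Abstract (Methods paragraph).** Safety means "zero or one patients in cohort 2 experiencing grade 3 or higher toxicity in the first 6 months post-treatment". This covers a period of time and one cohort.

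**Primary and secondary endpoints.** Phase I takes "12 patients: six patients in cohort 1 and six patients in cohort 2". The safety criterion is met when "no more than one patient in each cohort experiences a grade 3 or higher CTCAE V4.0 toxicity at 6 weeks or 6 months post-treatment". This names two time points and applies to both cohorts. Feasibility requires "10 or more of the planned 12 patients are successfully accrued and complete the study as per protocol within 24 months of activation". Both must be met before the trial expands to 30 men.

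**Translational exploratory endpoints.** This section dates the scorings: "CTCAE v4.0 toxicity scores and EPIC QoL scores will be done at 6 weeks and 6 months after the second treatment".

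**Treatment.** Cohort 2 receives Lu-177 first and HDR brachytherapy second. On timing: "In both cohorts, the time between the first treatment and the second will be 1–2 weeks". After Lu-177: "Patients will be monitored in an outpatient setting afterwards to assess for adverse events".

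Neither version of the safety rule says which treatment starts the clock. The text shown does not say how a man who receives Lu-177 but not HDR enters the safety count.

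**The concern.** The safety rule decides whether phase II opens, and with six men per cohort one man can reverse it. Its two wordings can give different answers on the same data, for three reasons:

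- **Period or visits.** A grade 3 event that starts and resolves between visits counts under the Abstract. It need not count under the Methods.
- **Start of the count.** If the 6-week and 6-month points run from the second treatment, the interval between Lu-177 and HDR lies before the first scoring. That is when early toxicity of the investigational agent would appear. A man who never receives HDR has no second treatment from which to date either visit.
- **One cohort or both.** Two events in cohort 1 stop expansion under the Methods but not under the Abstract.

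Laboratory follow-up adds to the second problem. The schedule names marrow, renal and hepatic bloodwork at 6 months after the second treatment. The Discussion lists lower blood counts and reduced renal function among the possible effects of Lu-177.

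At stake is a one-directional error: any event left out of the count moves the decision towards safe.

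**Working it through.** The article reports no error rates, power or calculated sample size, so there is no figure of its own to reproduce. The check sets out what the rules allow.

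**Inputs from the article.** Six men per cohort; at most one grade 3+ man per cohort; at least 10 of 12 completers, so at most 12 − 10 = 2 non-completers, from either cohort.

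**Step 1: worst case by counting.** If every event counts, the most that cohort 2 can have and still pass is 1 of 6. Suppose men who stop after Lu-177 with grade 3+ toxicity are not counted, both tolerated non-completers are such men, and all six in cohort 1 complete. Then:

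- completers: 6 + 4 = 10 of 12, so feasibility is met;
- counted events among the four completers in cohort 2: 1, so safety is met;
- true events in cohort 2: 2 + 1 = 3 of 6 (50%, exact 95% CI 12% to 88%).

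**Step 2: chance of passing if every event counts.** With true rate p,

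P(pass) = (1−p)^6 + 6p(1−p)^5.

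At p = 0.30: 0.1176 + 0.3025 = 0.420.

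**Step 3: chance of passing if early stops are not counted.** Let f be the share of affected men who stop before HDR. The article gives no value, so f is an assumption and is varied. Each man in cohort 2 is an uncounted stop (probability pf), a counted event (p(1−f)) or neither (1−p). The trial passes if stops ≤ 2 and counted events ≤ 1. Cohort 1 is taken to cause no failure, and there are no other drop-outs.

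At p = 0.30 and f = 0.25 the probabilities are 0.075, 0.225 and 0.70:

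| Stops | Counted | Probability |
|---|---|---|
| 0 | 0 | 0.1176 |
| 1 | 0 | 0.0756 |
| 2 | 0 | 0.0203 |
| 0 | 1 | 0.2269 |
| 1 | 1 | 0.1216 |
| 2 | 1 | 0.0260 |
| **Sum** | | **0.588** |

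The gain over Step 2 is 0.588 − 0.420 = 0.168. Most of it, 0.0203 + 0.1216 = 0.142, comes from passing with 2 of 6. Passing with 3 of 6 adds only 0.026.

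**Step 4: range.** The first two rates are the Discussion's figures for severe genitourinary toxicity after salvage HDR (9.6%) and for late grade 3 toxicity after salvage LDR (14%). They are illustrations, not rates for this combination.

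| True rate p | All counted | f = 10% | f = 25% | f = 50% |
|---|---|---|---|---|
| 9.6% | 0.894 | 0.911 | 0.936 | 0.968 |
| 14% | 0.800 | 0.831 | 0.875 | 0.933 |
| 20% | 0.655 | 0.704 | 0.774 | 0.870 |
| 30% | 0.420 | 0.487 | 0.588 | 0.733 |
| 40% | 0.233 | 0.300 | 0.408 | 0.570 |
| 50% | 0.109 | 0.162 | 0.256 | 0.402 |

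The chance of passing with exactly 3 of 6 is 0.005 to 0.069 at p = 30%, and 0.008 to 0.117 at p = 50%, for f from 10% to 50%.

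**Step 5: one cohort or both.** If both cohorts had a 9.6% rate and all events counted, the Abstract's rule would pass with probability 0.894. The Methods rule needs both cohorts to pass: 0.894 × 0.894, about 0.80.

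**The case against.** The strongest reply is that the article nowhere excludes early toxicity. Adverse events are monitored after Lu-177. The Abstract's period wording could take in those events, and the Methods rule itself says post-treatment without naming the second treatment. The sentence that does name it belongs to a visit schedule: it fixes when scores are taken, not which events count, nor whether the score is the current grade or the worst since last contact. Six men per cohort stand in the sentence before the rule as a natural denominator, and a man who received Lu-177 is still a cohort 2 patient. The two rules are not exclusive, so he could fail feasibility and count against safety, which leaves the limit at 1 of 6. Finally, a journal article condenses a fuller protocol, where the safety set may be defined.

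Much of this stands. A reader might infer that toxicity is scored only after the second treatment, or that men who stop early are feasibility drop-outs and not safety events. The documents support neither statement. A reader might also compare the rule on six men with the rule on four (0.351 against 0.593 at a one-third rate). That arithmetic is right, but it takes two losses as certain and leaves the remaining men's toxicity rate unchanged. It describes random loss, not loss caused by toxicity.

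The reply does not remove the conflict. The article states the primary safety rule twice, with a different window and a different scope. The only text shown that dates the scorings runs them from the second treatment. This is a contradiction in what is stated, not a detail left to another document.

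**Conclusion.** The point holds as an inconsistency in the primary decision rule, with a possible bias towards declaring safety. Abstract and Methods differ on period versus visits and on cohort 2 versus both cohorts. Taken literally with the follow-up schedule, the Methods version may leave out grade 3+ events before HDR, between visits, or in men who never receive HDR.

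The 3 of 6 figure is a conditional worst case. It needs both tolerated non-completers to be in cohort 2, both to have stopped with grade 3+ toxicity, neither to be counted, and all of cohort 1 to complete. It should not be read as what the plan prescribes. The more likely consequence, under the same reading, is passing with 2 of 6. The increase at a 30% rate, from 0.42 to between 0.49 and 0.73, rests on assumed early-stop shares of 10% to 50%.

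The dating and visit problems affect cohort 1 too. Confidence is moderate, because part of the Methods between the treatment description and the endpoints was not available and could hold a relevant rule. Even so, the wording should be settled before the phase I decision.

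**What to change.** Reconcile the Abstract, the primary endpoint paragraph and the follow-up schedule so that all three carry one rule, applied in each cohort:

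- The safety set is every patient who received any study treatment.
- A patient counts if his worst CTCAE grade is 3 or higher at any time from the start of the first treatment to 6 months after the last treatment he received.
- A patient without a second treatment stays in the count, with his 6-week and 6-month assessments dated from the last treatment given. He may also be a non-completer for feasibility.
- Events found in the monitoring after Lu-177 feed this count.

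This changes how the endpoint is counted and leaves treatment and clinical management as they are. It costs about two sentences in an amendment, plus follow-up assessments for men who stop early; the monitoring after Lu-177 is already planned. The chance of passing the safety rule falls by an amount that depends on how many toxicities occur early: at a 30% rate, from 0.59 to 0.42 if a quarter of affected men would otherwise have gone uncounted. If the investigators already intend to count such events, the men who stop early make no difference to that chance, and the amendment mainly records the intention.
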